Introducing a screen-and-treat strategy that combines these innovations—self-sampling, rapid HPV assays, and thermal ablation—promises to improve screening and treatment rates in resource-limited settings including Malawi. However, success requires considering key implementation questions around how to target healthy women and how to reach rural women who have poor access to health facilities. Integrating cervical cancer screening with family planning (FP) services is a promising strategy because many women who access FP services are in the appropriate screening age range and sexually-active. Existing structures to deliver community-based FP services can be utilized to reach women in rural and isolated areas. Any solution for increasing CCSPT services in sub-Saharan Africa must be applicable to rural populations, since an estimated 60–75% of women who develop cervical cancer in sub-Saharan Africa live in rural areas [14].

In many countries, community health workers provide a vital link between health facilities and rural populations. Community-based FP services have been effective in increasing FP uptake in many countries [15], including in Malawi where 80% of the population is rural [16, 17]. Community health workers in Malawi, known as health surveillance assistants (HSAs), provide FP services to rural women through outreach and village clinics. Experience from other countries suggests that community health workers like HSAs can be successfully trained to offer self-sampling for HPV screening in rural areas [18, 19]. However, providing community-based screening introduces additional challenges for follow-up given that same-day screening and treatment will not be conducted. Understanding the impact of community-based screening on loss to follow-up is important given that one of the primary shortcomings in Malawi’s CCSPT program has been the low rate of treatment among screen-positive women. Thermal ablation may be more scalable than cryoablation but would only improve access if women are successfully informed of their results and linked to care at facilities.

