**Table 1 Tab1:**
[figure not shown]
Work plan

The pre-implementation period will be used for obtaining ethical approvals, developing study-specific forms and procedures, selecting and randomizing facilities, and preparing facilities to offer the new services through equipment procurement, facility rehabilitation, and training. We will also complete time-and-motion evaluations and the first round of mixed methods assessments, involving interviews, focus groups, and surveys, to understand the baseline situation. During the implementation period, we will perform additional rounds of mixed methods assessments and collect routine service utilization data from each facility. Assessment details are provided in Table 2. Near the end of the implementation period, we will conduct an Endline Household Survey to assess uptake of CCSPT and FP services among women who live in the catchment areas of the health facilities. The Endline Household Survey will allow us to compare the screening and treatment rates of the clinic-only and the clinic-and-community model.

**Table 2 Tab2:** Descriptions of assessments, organized by objective

Assessment	Description	Participants	Sample size
Objective 1: Compare the proportion of eligible women who receive CCSPT and FP services in the catchment areas of health facilities assigned to the two models.			
Endline Household Survey	The survey covers prior and recent use of CCSPT and FP services.	Women residing in the catchment areas for the health facilities; must be aged 15–50 years and cannot have had their cervix removed.	8000 women
Objective 2: Assess the acceptability, appropriateness, and feasibility of the two models among key stakeholders, including providers, facility management teams, and clients			
Baseline Assessment Form	The form collects information about the facility’s capabilities for providing CCSPT and FP services.	Completed by research assistants, one form per facility	16 forms (one per facility)
Readiness Assessment Forms	The form includes Likert scale rankings for various parameters of the readiness of the facilities/health system to implement the two models. Participants will answer the survey in small groups, coming to consensus on each ranking.	District health management team members, health facility managers, and community stakeholders	16 forms (one per facility)

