### Description of models

In both model 1 and model 2, through group educational talks and one-on-one counseling, women will be educated about cervical cancer screening and the opportunity to perform self-sampling for HPV testing. The facility staff will be encouraged to hold the CCSPT educational talks in waiting rooms for the FP clinic, antiretroviral therapy (ART) clinic, and other clinics.

Once a woman presents to the CCSPT clinic at the facility, she will be offered self-collection if she meets the following eligibility criteria: (1) aged 25–49 years old, (2) no history of total hysterectomy, (3) no history of cervical cancer, and (4) not currently pregnant. Self-collected samples will then be sent to the facility laboratory for high-risk HPV (hrHPV) testing using the GeneXpert® (Cepheid Inc, Sunnyvale, CA, USA) platform. We chose to use the Xpert HPV assay because it offers several advantages over other commercially available HPV assays: results are available within 1–2 h, all reagents are contained in one cartridge, and laboratory personnel only need a short training course to use the machines. In addition, the Xpert HPV assay has been validated in Malawi, and many facilities in Malawi have already invested in Xpert machines for tuberculosis diagnostic testing [27].

Women who screen positive for hrHPV at the clinic will be offered same-day VIA to determine whether they are eligible for ablative treatment. Eligibility for thermal ablation requires that (1) no cervical lesions or any visible lesion covers <75% of the cervix and can be seen in its entirety, (2) the lesion does not extend into the endocervical canal or to the vaginal wall, (3) the squamocolumnar junction is visible, (4) the client is more than 3 months postpartum if recently pregnant, (5) there is no suspicion of cervical cancer, (6) there are no polyps or scarring impeding contact of the probe, and (7) there is no evidence of current menstruation or cervicitis. HPV-positive and treatment-eligible women will be offered thermal ablation on the same day of screening.

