In model 2, women living in the health facility’s catchment area will also be offered self-sampling in the community. HSAs and other health facility staff will give educational talks about self-sampling to groups of women at village and outreach clinics. Interested women can perform self-sampling on the day of the community clinic, and HSAs will transport the sample back to the health facility for testing. Women can receive results at the next community clinic or by presenting to the associated health facility. If any women screens HPV-positive, she will be referred for VIA and possible treatment. Patient flow is illustrated in Fig. 2, with light blue shading for the community-based components.

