### Analysis plan

#### Endline Household Survey

Key outcomes from the Endline Household Survey include (1) the proportion of eligible women who have received CCS during the 18 months of study implementation, (2) the proportion of treatment-eligible women who received thermal ablation during the study period, and (3) the proportion of women aged 15–50 years who are using a modern FP method. These proportions will be calculated using descriptive statistics. Differences between the clinic-only and clinic-and-community models will be assessed via logistic regression, adjusted for district, facility size, and facility type. The regression model will account for health facility clustering, and analyses will be adjusted for the small number of clusters [28, 29].

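### The between-model treatment comparison is confined to treatment-eligible women, a group formed after randomisation; it can show the models as equal while model 2 treats more women

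*Protocol article*

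**What the plan says.** In the Analysis plan, under Endline Household Survey, three key proportions are listed. The first uses all eligible women as its denominator: "the proportion of eligible women who have received CCS during the 18 months of study implementation". The second does not: "the proportion of treatment-eligible women who received thermal ablation during the study period". The third concerns modern family planning use. The plan then states: "Differences between the clinic-only and clinic-and-community models will be assessed via logistic regression, adjusted for district, facility size, and facility type". Nothing exempts the second proportion from that comparison.

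Description of models shows how a woman becomes treatment-eligible. At the facility: "Women who screen positive for hrHPV at the clinic will be offered same-day VIA to determine whether they are eligible for ablative treatment". After community sampling, which exists only in model 2: "If any women screens HPV-positive, she will be referred for VIA and possible treatment".

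The Background gives the reason for interest in this step: "Understanding the impact of community-based screening on loss to follow-up is important". The Design section says the survey will serve to "compare the screening and treatment rates of the clinic-only and the clinic-and-community model". Table 2 words Objective 1 as a comparison, among eligible women in the catchment areas, of receipt of screening and preventive treatment together with family planning.

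**The concern.** Randomisation makes the women living in the two sets of catchment areas comparable. It does not do so for women who were screened, tested positive and were found suitable for ablation at VIA. Model 2 adds community sampling precisely to bring in women whom clinics do not reach, so the two treatment-eligible groups differ by design. District, facility size and facility type describe facilities and cannot adjust for which women enter the group.

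Two consequences follow.

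- The comparison gives no credit for the additional women model 2 brings to treatment.
- If eligibility is fixed at VIA, a woman who tests positive in the community and never attends VIA drops out of the denominator. That is the loss the Background and Discussion worry about.

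The results are meant to inform policy. A reader could be told that the models do not differ on treatment when one of them treats appreciably more women.

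**Working it through.** **The plan's own figure.** The only stated power concerns screening: at least 83% for a 30-point difference from 40%, with 7 facilities per arm, mean size 3400, ICC 0.15 and CV 0.35 (Sample size calculations). Assuming two-sided alpha 0.05:

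- Design effect: 1 + ((0.35² + 1) × 3400 − 1) × 0.15 = 573.3.
- Effective size per arm: 7 × 3400 / 573.3 = 41.5.
- SE: √((0.40 × 0.60 + 0.70 × 0.30) / 41.5) = 0.104.
- z = 0.30 / 0.104 − 1.96 = 0.92, so power is about 82%.

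This agrees with the article. No figure is given for the treatment outcome.

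**Inputs for the treatment cascade.**

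- Screened: 40% v 70%, the power scenario above.
- HPV-positive: 20% (assumed).
- VIA attended: 90% of clinic-screened positives (assumed) and 50% of the added community-screened positives (assumed; the Discussion cites a pilot in which over half of such women could not be reached by telephone).
- Ablation-eligible at VIA: 80% (assumed).
- Treated if eligible: 90% (assumed).
- Community screening adds to clinic screening (assumed; relaxed below).

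**Per 10,000 eligible women:**

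| Step | Model 1 | Model 2 |
|---|---|---|
| Screened | 4000 | 4000 + 3000 = 7000 |
| HPV-positive | 800 | 800 + 600 = 1400 |
| Reached VIA | 720 | 720 + 300 = 1020 |
| Treatment-eligible | 576 | 576 + 240 = 816 |
| Treated | 518.4 | 518.4 + 216 = 734.4 |

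- Treated/treatment-eligible (the plan's outcome): 518.4/576 = 90.0% v 734.4/816 = 90.0%, odds ratio 1.00.
- Treated/HPV-positive: 518.4/800 = 64.8% v 734.4/1400 = 52.5%.
- Treated/all eligible women: 5.2% v 7.3%, odds ratio about 1.45.

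The plan's outcome shows neither the poorer linkage (second line) nor the larger number treated (third line).

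**When model 2 looks worse.** Lower treatment among eligible community-screened women to 80%. Model 2 then treats 518.4 + 192 = 710.4 women. The outcome is 90.0% v 710.4/816 = 87.1% (odds ratio about 0.75), while 5.2% v 7.1% of all eligible women are treated (odds ratio about 1.40).

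**Room before the totals reverse.** With 816 eligible in model 2, its conditional proportion would have to fall to 518.4/816 = 63.5% for equal totals. If both models had the same eligible fraction per woman screened, the figure is 0.90 × 0.40/0.70 = 51.4%.

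**Sensitivity.** The plan's outcome stays at 90% v 90% in each case below, and the share of all eligible women treated changes as shown.

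- Community VIA attendance 43%: 5.2% v 7.0%.
- Screening 40% v 75%: 5.2% v 7.7%.
- Screening 50% v 80%: 6.5% v 8.6%.
- Positivity 30% and ablation-eligible 90%: 8.7% v 12.4%.
- Some clinic screening replaced by community screening: with c of model 2's 7000 screened at clinics, treated = 0.20 × 0.80 × 0.90 × (0.9c + 0.5(7000 − c)). This equals 518.4 only at c = 250, so model 2 treats more unless clinic screening falls from 4000 to below 250.

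**The case against.** The best defence is that the conditional proportion answers a question the trial asks. The Background and Discussion frame the treatment problem as a rate among screen-positive women (43% nationally), and the trial wants to know whether linkage suffers after community screening. Treated/all women mixes uptake with linkage: a model with poor linkage could look better merely by screening more. The screening and treatment proportions will be reported together, no treatment hypothesis is stated, and the primary outcome is uptake of screening and family planning. This stands as a reason to keep the conditional proportions as description. It does not make a regression between models on this denominator a randomised comparison. Read strictly, the plan's denominator is also not the one that captures linkage, since the losses occur before VIA.

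A reader might infer more than the documents support:

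- That model 2 would look far worse on this outcome. The large gap (64.8% v 52.5% above) arises with HPV-positive women as the denominator, which is not what the plan specifies. On the plan's denominator the models look alike unless treatment after VIA also differs.
- That 40% and 70% are the planned screening rates. They are a floor and that floor plus the detectable difference; the article expects at least 40–50% and hopes to approach 80%.
- That the trial never intended a catchment-wide treatment outcome. Table 2's Objective 1 points to one, and the list of key outcomes need not be exhaustive. The fault is that the analysis plan does not carry that denominator into the treatment outcome it does specify.

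**Conclusion.** The point holds for a key, non-primary outcome. The treatment comparison conditions on a status acquired after randomisation through steps that model 2 is designed to alter, and the listed covariates do not address that selection. In the worked scenario it reports 90% v 90% while model 2 treats 734.4/518.4 = 1.42 times as many women (5.2% v 7.3% of all eligible women). It ranks model 2 lower (90% v 87%) only under the further assumption of poorer treatment among eligible community-screened women.

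The sizes rest on assumed positivity, VIA attendance, ablation eligibility and treatment rates, since the article gives none for this trial. With positivity and ablation eligibility equal in both models, the direction does not depend on their values. The screening and family planning comparisons, and the stated power, are untouched.

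**What to change.** In the Analysis plan, under Endline Household Survey:

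1. Define the between-model treatment outcome as the proportion of all screening-eligible women surveyed in the catchment areas who received thermal ablation during implementation. Analyse it with the same cluster-adjusted logistic model. This agrees with Objective 1 in Table 2.
2. Report treated/HPV-positive and treated/treatment-eligible by model as descriptive cascade measures of linkage, not as estimates of the model effect.

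The cost is a change of analysis wording. The survey is already planned to record screening and treatment services received during implementation from sampled women, screened or not. The drawback is that the new outcome is a small percentage, combines uptake with linkage and varies with HPV prevalence (the Setting section expects regional variation in burden), so it should be read beside the cascade steps.

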**Methods:**

We designed a cluster randomized feasibility trial to determine the effectiveness, acceptability, appropriateness, feasibility, and budget impact of two models for integrating a HPV-based CCSPT program into family planning (FP) services in Malawi: model 1 involves only clinic-based self-sampled HPV testing, whereas model 2 includes both clinic-based and community-based self-sampled HPV testing. Our algorithm involves self-collection of samples for HPV GeneXpert® testing, visual inspection with acetic acid for HPV-positive women to determine ablative treatment eligibility, and same-day thermal ablation for treatment-eligible women. Interventions will be implemented at 14 selected facilities. Our primary outcome will be the uptake of cervical cancer screening and family planning services during the 18 months of implementation, which will be measured through an Endline Household Survey. We will also conduct mixed methods assessments to understand the acceptability, appropriateness, and feasibility of the interventions, and a cost analysis to assess budget impact.

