## Methods/design

### Aims and objectives

Our aim is to compare the effectiveness, acceptability, appropriateness, feasibility, and budget impact of integrating self-sampled HPV testing into FP services via clinics only versus including community-based screening.

Our specific objectives are as follows:
Compare the effectiveness of our two models on uptake of CCS and FP services among eligible women in the catchment areas of health facilities assigned to the two models. The effectiveness will be evaluated through analysis of an Endline Household Survey, which will be administered to randomly selected eligible women in the catchment areas of the health facilities at the end of project implementation.
We hypothesize that the proportion of eligible women who have received CCS services during the 12 months of project implementation will be higher among eligible women in the catchment areas of health facilities assigned to model 2 than in model 1.We hypothesize that the proportion of eligible women who have received FP services during the 12 months of project implementation will be higher among eligible women in the catchment areas of health facilities assigned to model 2 than in model 1.Assess the acceptability, appropriateness, and feasibility of the two models among key stakeholders, including providers, facility management teams, and clients. These implementation outcomes will be evaluated through analysis of mixed methods assessments, including use of quantitative tools (Acceptability-Appropriateness-Feasibility Tool, Client Exit Survey) as well as qualitative interviews with providers, facility management teams, and clients.
We hypothesize that both models will be viewed as acceptable and appropriate by health care providers, facility management teams, and clients.We hypothesize that both models will be feasible in a variety of health facilities in Malawi.Estimate the cost and budget impact of each model compared to the standard-of-care (VIA and cryotherapy). These outcomes will be evaluated through analysis of structured observations during time-and-motion studies, the Workload Assessment Tool, and cost expenditures during implementation of the study.
We hypothesize that both models will be more cost-effective than the current standard-of-care for the number of cervical cancer case averted.We hypothesize that model 1 will be more cost-effective than model 2.

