### Sample size calculations

Sample size calculations were based on the ability to detect a difference in service uptake through the Endline Household Survey. As noted earlier, only 26.5% of Malawian women had been screened at least once in their lifetime as of 2015 with use of VIA for primary screening [3], which is much lower than the targeted rate of 80% set at the onset of Malawi’s Cervical Cancer Control Program in 2004 [16]. We estimated that with the introduction of HPV self-sampling in our clinic-only arm, at least 40–50% of eligible women in our facility catchment areas will be screened during our 18 months of implementation. We then estimated that with the addition of HPV self-sampling in the community to reach rural women, we would be able to approach Malawi’s targeted rate of 80% of eligible women screened in our clinic + community arm. Based on data obtained from potential facilities in Lilongwe and Zomba, we also estimated an average cluster size of 8000 eligible women per health facility and a coefficient of variation of the cluster sizes of 0.35. Finally, we estimated that our intra-cluster correlation coefficient (ICC) will be between 0.12 and 0.19, based on other similar studies performed in Malawi, where the ICC ranged from 0.004 to 0.20 [25, 26]. With 16 randomized facilities (8 per arm), we initially estimated that we would have at least 80% power to detect a difference of at least 25–30% between our 2 arms, even if the proportion of women screened in the clinic-only arm is as low as 40%. For example, if the clinic-only arm found that 40% of women had been screened, we would have 80% power to detect a difference if the clinic + community arm had screened at least 75% of women in their catchment areas.

However, after performing site selection and randomization, we learned that the two central/district hospitals selected could not be assigned to model 2 as their HSAs did not perform community-based services. Therefore, we dropped these 2 hospitals from our sample size calculations and decreased our average cluster size to 3400 eligible women accordingly. With an ICC of 0.15 and coefficient of variation of cluster sizes of 0.35, we will have at least 83% power to detect of difference of at least 30% between our 2 arms (with 7 facilities in each arm), even if the proportion of women screened in the clinic-only arm is as low as 40%. All power calculations were calculated in R (Version 3.5.1, clusterPower package).

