#### Endline Household Survey

The Endline Household Survey, conducted at months 13–15 after implementation, will be the primary tool to assess the uptake of CCSPT and FP services among women in the catchment areas of the health facilities. Households will be sampled in a two-stage sampling design. Stage 1 will include a random sample of enumeration areas (EAs) from all of the facilities’ catchment areas. This random sample will be selected with the number of EAs proportional to the size of the catchment area. In each selected EA, we will undertake a household listing to create a sampling frame of households for the survey. In stage 2, a random sample of households will be selected. Our target sample size is up to 8000 women aged 15–50 years from the 16 health facility catchment areas. The age range is intended to include women most likely to utilize FP services, as well as those in the target range for CCSPT. With the expectation of ~1.1 women aged 15–50 in our households, the sample will include ~8000 households selected from 266 EAs selected proportionally from facility catchment areas (randomly selecting ~30 households/EA). Parental consent will be obtained for participants 15–17 years old, as described in the “Ethical considerations” section. If a randomly sampled woman does not consent for the survey, she will be replaced with another randomly selected woman from her EA.

Women aged 15–50 years will be eligible to participate in the interviewer-administered survey, provided that they have not had their cervix removed. The survey will cover demographic information, reproductive health information, HIV status, distance to the nearest health facility, prior FP use, FP use during project implementation, prior CCSPT services received, and CCSPT services received during project implementation.

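### The family planning outcome in the analysis plan is current modern-method use, which does not test the stated hypothesis about family planning services received during implementation

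*Protocol article*

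**What the plan says.** The protocol article describes the FP outcome in four places.

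- Abstract, Methods: "Our primary outcome will be the uptake of cervical cancer screening and family planning services during the 18 months of implementation".
- Aims and objectives, Objective 1: the FP hypothesis is that model 2 exceeds model 1 on "the proportion of eligible women who have received FP services during the 12 months of project implementation". Table 2 likewise words Objective 1 in terms of women who receive services.
- Analysis plan, Endline Household Survey: the FP outcome is "the proportion of women aged 15–50 years who are using a modern FP method". The screening outcome in the same list is "the proportion of eligible women who have received CCS during the 18 months of study implementation".
- Assessments, Endline Household Survey: the questionnaire is to cover "prior FP use, FP use during project implementation, prior CCSPT services received, and CCSPT services received during project implementation".

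On power, the Sample size calculations section opens with "Sample size calculations were based on the ability to detect a difference in service uptake through the Endline Household Survey", but every rate that follows is a screening rate.

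**The concern.** Uptake of a service over a period and use of a method on the day of interview are different quantities. The first counts events that the two models could have caused. The second is a prevalence that includes methods obtained before launch and leaves out women who were served and later stopped. FP is named in the primary outcome and has its own directional hypothesis. If the analysis plan is followed as written, the FP result will not answer that hypothesis, and a reader could take a difference, or its absence, in current use as evidence about service uptake. In addition, the general opening of the sample size section could lead a reader to believe that the 83% power covers FP as well.

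**Working it through.** **1. The definitions side by side**

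| Feature | Abstract and Objective 1 (FP) | Analysis plan (FP) | Analysis plan (screening) |
|---|---|---|---|
| What is counted | services taken up or received | current use of a modern method | screening received |
| Window | 18 months (abstract), 12 months (Objective 1) | none | 18 months |
| Denominator | eligible women | women aged 15–50 | eligible women |

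Only FP changes its nature between hypothesis and analysis.

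**2. How each measure classifies a woman**

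| Woman | Service received in window | Current modern use |
|---|---|---|
| Long-acting or permanent method from before launch, no service since | no | yes |
| Received FP in the window, stopped before interview | yes | no |
| Received FP in the window, still using a modern method | yes | yes |
| Neither received nor uses | no | no |

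The first two rows are discordant. The document gives no figures for how many women fall in them.

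**3. The plan's own power figure**

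Inputs from Sample size calculations: 40% against 70%, m = 7 facilities per arm, n = 3400 women per facility, CV 0.35, ICC 0.15. Two-sided 5% is my assumption, since the article states no alpha.

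- Design effect: DEFF = 1 + [(CV²·(m−1)/m + 1)·n − 1]·ICC. Here CV²·(m−1)/m = 0.1225 × 6/7 = 0.105, so DEFF = 1 + (1.105 × 3400 − 1) × 0.15 = 564.4.
- SE = √{[p₁(1−p₁) + p₂(1−p₂)]·DEFF/(m·n)} = √{(0.24 + 0.21) × 564.4/23,800} = 0.1033.
- Power = Φ(0.30/0.1033 − 1.96) = Φ(0.944) = 82.7%, in agreement with the stated 83%.

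The inputs are all screening inputs: 26.5%, 40–50%, 75% and 80% are screening proportions. The section has no FP rate, FP effect or FP ICC.

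**4. What the same design gives for FP**

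Assumptions: control rate 30–60%, a 10-point difference, 7 facilities per arm, and about 500 women per facility (8000/16, from the survey description). The ICC is varied over the range the article cites from similar studies, 0.004 to 0.20.

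Example at ICC 0.15 and 45% against 55%: DEFF = 1 + (1.105 × 500 − 1) × 0.15 = 83.7. SE = √{(0.2475 + 0.2475) × 83.7/3500} = 0.109. Power = Φ(0.10/0.109 − 1.96) = Φ(−1.04) = about 15%.

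| ICC | Power for 10 points | Detectable difference at 80% power |
|---|---|---|
| 0.004 | over 99% | about 6 points |
| 0.02 | 68–72% | about 11 points |
| 0.05 | 35–38% | 16–18 points |
| 0.15 | 15–16% | 26–29 points |
| 0.20 | 12–13% | 29–33 points |

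The answer depends almost entirely on an FP ICC that the article does not give.

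**The case against.** The strongest reply is that this is a condensed article about a feasibility trial. The analysis plan says the key outcomes include three items, so the list is not closed, and a service-receipt analysis may exist in the fuller plan. That is fair, but the article fixes one FP outcome, and it disagrees with the article's own primary outcome and hypothesis. That is a contradiction within the text rather than a detail left out.

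A second reply is that the existing questionnaire may not rescue the intended definition. It speaks of FP use during implementation, whereas for cervical services it speaks of services received. An implant placed before launch is also use during implementation. This stands, and it qualifies the fix.

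A reader might also infer three stronger points that the document does not support.

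- **Current use dilutes the effect and counting receipt would cure it.** If a share f of women (assume 10–30%) hold a method from before launch and need no further service, a 10-point gain among the rest becomes 10 × (1 − f) = 9 to 7 points. Under current use these women are fixed successes; under receipt, with the same denominator, they are fixed failures. The arithmetic is the same either way.
- **The false-positive rate rises to 9.75%.** The figure is 1 − 0.95². It needs independent tests, a 5% level and a rule that success on either outcome suffices. The article states neither the level nor the rule, and a statistical analysis plan not shown may settle both. For the same reason, testing FP only after screening succeeds is a design preference and not the correction of an error.
- **FP is hopelessly underpowered.** That requires lending FP the ICC of 0.15 chosen for screening. Powering a feasibility trial on one outcome is also ordinary practice.

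**Conclusion.** The definition mismatch holds on the text alone and needs no numerical assumption: the FP outcome as analysed does not test the FP hypothesis as stated. Its numerical effect cannot be given, because the article has no data on methods obtained before launch or on discontinuation. The screening comparison is unaffected.

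The power statement supports screening uptake only. For FP, power for a 10-point difference lies anywhere from about 12% to over 99%, given 7 facilities per arm, about 500 women each, CV 0.35, control rates of 30–60%, two-sided 5%, and ICCs from 0.20 down to 0.004. This shows that no FP power has been established; it does not show that FP power is low. The point should be dealt with before the endline survey is fielded, while the questionnaire can still be altered.

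**What to change.** - In the analysis plan, define the FP outcome as receipt of an FP service within the same fixed window as screening.
- Reconcile the 12 months in Objective 1 with the 18 months in the abstract and analysis plan. The survey is scheduled for months 13–15; if these are counted from the start of implementation, a full 18 months cannot have been observed at interview, so the window must be one the survey can cover.
- State the FP denominator: either eligible women, with eligibility for FP defined, or all women aged 15–50.
- Confirm that the survey items capture receipt of a service and its timing, and add one question if they record only use.
- Keep current modern-method use as a secondary outcome.
- State in Sample size calculations that the 83% applies to screening uptake only.

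The cost is wording, plus possibly one added survey question. The number of facilities and the survey size do not change.
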